## 9.3 Recording and reporting of SAEs, SARs AND SUSARs

The time-frame over which ARs and SAEs are recorded is described in section 9.2.

ARs are recorded on the case-report forms. If the AR is serious, it will also be captured on the SAE form. SAEs not related to the study medication will also be captured on the SAE form. When an SAE or SAR occurs, it is the responsibility of the Investigator to review all documentation (e.g. hospital notes, laboratory and diagnostic reports) related to the event. The Investigator should then record all relevant information on the SAE form. The SAE will collect information on diagnosis, dose, type of event, onset date, Investigator assessment of severity and causality, date of resolution, as well as any treatment required, action taken, investigations needed and outcome.

Once the Investigator becomes aware that an SAE has occurred in a study participant, they must report the information to the Trial Office within 24 hours of becoming aware of the event, the Trial Office will report to the Sponsor within 24 hours of becoming aware of the event as per the current Sponsor SOP (SOP-QA-22).

The SAE form must be completed as thoroughly as possible (either as a hard copy CRF or electronically on the trial website) with all available details of the event, and signed by the Investigator or designee. The completed SAE form should then be faxed or emailed to the study office.

If all the required information is not available at the time of reporting, the Investigator must ensure that any missing information is provided as soon as this becomes available. It should be indicated on the report that this information is follow-up information of a previously reported event.

For the purposes of this study, the Reference Safety Information used in the assessment of expectedness is section 4.8 of the SmPC for bisoprolol. This can be found on the study website.

All SAEs assigned by the PI or delegate (or following central review) as both suspected to be related to IMP-treatment and unexpected will be classified as SUSARs and will be subject to expedited reporting to the

Medicines and Healthcare Products Regulatory Agency (MHRA). The sponsor will inform the MHRA, the REC and Marketing Authorisation Holder (if not the sponsor) of SUSARs within the required expedited reporting timescales.

#### **9.4 Responsibilities**

##### Principal Investigator (PI):

- Checking for ARs and SAEs when participants attend for treatment / follow-up. This may be delegated to other members of the research team at site.
- Using medical judgement in assigning seriousness, causality and whether the event/reaction was anticipated using the Reference Safety Information approved for the trial.
- Ensuring that all SAEs and SARs are recorded and reported to the trial office within 24 hours of becoming aware of the event and provide further follow-up information as soon as available.
- Ensuring that SAEs and SARs are recorded and reported to the sponsor in line with the requirements of the protocol.

##### Chief Investigator (CI) / delegate or independent clinical reviewer:

- Clinical oversight of the safety of patients participating in the trial, including an ongoing review of the risk / benefit.
- Using medical judgement in assigning the SAEs seriousness, causality and whether the event was anticipated (in line with the Reference Safety Information) where it has not been possible to obtain local medical assessment.
- Immediate review of all SUSARs.
- Assigning Medical Dictionary for Regulatory Activities (MedDRA) or Body System coding to all SAEs and SARs.
- Preparing the clinical sections and final sign off of the Development Safety Update Report (DSUR).

##### Trial manager

- Central data collection of ARs, SAEs, SARs and SUSARs according to the trial protocol onto a database.
- Reporting safety information to the CI, delegate or independent clinical reviewer for the ongoing assessment of the risk / benefit.
- Reporting safety information to the independent oversight committees identified for the trial (Data Monitoring Committee (DMC) and / or Trial Steering Committee (TSC)).
- Expedited reporting of SUSARs to the Competent Authority (MHRA in UK) and REC within required timelines.
- Notifying Investigators of SUSARs that occur within the trial.
- The unblinding of a participant for the purpose of expedited SUSAR reporting.
- Checking for updates to the Reference Safety Information for the trial.
- Preparing standard tables and other relevant information for the DSUR in collaboration with the CI and ensuring timely submission to the MHRA and REC.

##### Trial Steering Committee (TSC):

In accordance with the Terms of Reference for the TSC, periodically reviewing blinded safety data and liaising with the DMC regarding safety issues.

##### Data Monitoring Committee (DMC):

In accordance with the Terms of Reference for the DMC, periodically reviewing overall safety data to determine patterns and trends of events, or to identify safety issues, which would not be apparent on an individual case basis. The DMC may review safety data in an unblinded fashion.

## 9.5 Notification of deaths

All deaths will be reported to the sponsor irrespective of whether the death is related to disease progression, the IMP, or an unrelated event. The standard SAE form should be used to report deaths. Once the Investigator becomes aware that a death has occurred in a study participant, they must report the information to the Trial Office within 24 hours of becoming aware of the event, the Trial Office will report to the Sponsor within 24 hours of becoming aware of the event as per the current Sponsor SOP (SOP-QA-22).

## 9.6 Pregnancy reporting

The SmPC for bisoprolol states that it should not be used during pregnancy or whilst lactating unless clearly necessary. Current (or planned pregnancy during the study) or current breastfeeding are exclusion criteria, although given the age profile of people with COPD this is unlikely to be a major issue (see section 9.6.1 for contraceptive requirements and pregnancy testing).

Pregnancy is not considered an SAE however the investigator must collect pregnancy information for female trial subjects. The Investigator should record the information on a Pregnancy Notification Form and submit this to the Trial Office within 14 days of being made aware of the pregnancy. In such cases, trial medication should be stopped. Any pregnancy that occurs in a trial subject during a trial should be followed to outcome. In some circumstances, it may be necessary to monitor the development of the newborn for an appropriate period post delivery. Should the trial subject not wish for the pregnancy to be followed to outcome or beyond, this should be noted in the CRF and medical notes as appropriate.

### 9.6.1 Contraceptive requirements and pregnancy testing

Women who are eligible to take part in the trial and are of child bearing potential (i.e. are not post-menopausal (defined as 12 months with no menses without an alternative medical cause) or permanently sterilised) will be advised to use two forms of highly effective birth control (i.e. results in a less than 1% per year failure rate) and continue use until at least 28 days after last dose of trial medication. Acceptable forms of contraception include:-

- Established use of oral, transdermal, injected or implanted hormonal methods of contraception.
- Placement of an intrauterine device (IUD) or intrauterine system (IUS).
- Barrier methods of contraception: Condom or Occlusive cap (diaphragm or cervical/vault caps) plus a spermicidal foam/gel/film/cream/suppository.
- Male partner is sterile (with the appropriate post-vasectomy documentation of the absence of sperm in the ejaculate) prior to female entry onto the trial and is the sole partner of the female participant.
- True abstinence: When this is in line with the preferred and usual lifestyle of the subject. [Periodic abstinence (e.g., calendar, ovulation, symptothermal, post-ovulation methods) and withdrawal are not acceptable methods of contraception for trial purposes].

Women who are of child bearing potential should have a pregnancy test seven days or fewer before the first dose of study medication. For women who attend a face-to-face recruitment visit, the pregnancy test can be conducted then. For women recruited without a face-to-face recruitment visit, a pregnancy test can be sent at the same time as the sphygmomanometer and women will be asked to report the results of the pregnancy test during the recruitment assessment. Women of child bearing potential should also have a pregnancy test at the end of titration and at the 6 and 12 month assessments. Women will be sent the pregnancy test around the time of the visit and be asked to report the results of the pregnancy test to the research nurse.

The SmPC for bisoprolol does not warn against the use of bisoprolol in men because of teratogenic effects [35]. No contraception measures are needed for male subjects with pregnant or non-pregnant partner.

## 9.7 Overdose

To date a few cases of overdose (maximum: 2000 mg as a single dose (equivalent to 1600 1.25mg tablets) with bisoprolol have been reported in patients suffering from hypertension and/or coronary heart disease showing bradycardia and/or hypotension; all patients recovered [35]. The maximum total dose of bisoprolol sent out to participants at any one time is 840mg (672 1.25mg tablets).

With overdose (e.g. daily dose of 15 mg instead of 5 mg) third degree AV-block, bradycardia, and dizziness have been reported. In general, the most common signs expected with overdose of a beta-blocking agent are bradycardia, hypotension, bronchospasm, acute cardiac insufficiency and hypoglycaemia.

In general, if overdose occurs, bisoprolol treatment should be stopped and supportive and symptomatic treatment should be provided. Limited data suggest that bisoprolol is hardly dialysable. Based on the expected pharmacologic actions and recommendations for other beta-blocking agents, the following general measures should be considered when clinically warranted.

**Bradycardia:** Administer intravenous atropine. If the response is inadequate, isoprenaline or another agent with positive chronotropic properties may be given cautiously. Under some circumstances, temporary pacing may be necessary.

**Hypotension:** Intravenous fluids and vasopressors should be administered. Intravenous glucagon may be useful.

**AV block (second or third degree):** Patients should be carefully monitored and treated with isoprenaline infusion or temporary pacing may be necessary.

**Heart failure:** Administer i.v. diuretics, inotropic agents, vasodilating agents.

**Bronchospasm:** Administer bronchodilator therapy such as isoprenaline, beta2-sympathomimetic medicinal products and/or aminophylline.

**Hypoglycaemia:** Administer i.v. glucose.

All overdoses will be reported to the sponsor, overdoses will be evaluated on a case by case basis and decisions to withdraw/retain in the trial cases will be made depending on the degree of unblinding/individual circumstances/participant safety.

## 9.8 Reporting urgent safety measures

If any urgent safety measures are taken the CI/Sponsor shall telephone the MHRA's Clinical Trial Unit as soon as possible after the action is implemented and discuss the issue. Within three days of the date the measures are taken, the CI/Sponsor will give written notice to the MHRA and the relevant REC of the measures taken and the circumstances giving rise to those measures.

## 9.9 The type and duration of the follow-up of participants after adverse reactions.

After initially recording and reporting an AR or an SAE, the Investigator is required to follow each participant as indicated by clinical practice. Follow up information on an SAE should be reported to the Sponsor as per the current SOP (SOP-QA-22).

Section 9.2 of the protocol describes the time-frame over which adverse reactions and SAEs need to be recorded.

### 9.10 Development safety update reports

An annual Development Safety Update Report (DSUR) will be submitted to the MHRA and the main REC listing all SARs and SUSARs. The Chief Investigator is responsible for preparing and submitting annual DSURs to the MHRA and the main REC on the anniversary of the Clinical Trial Authorisation approval.

### 9.11 Incidental findings

Any incidental findings that are clinically important will be communicated to the participant's GP and to the participant themselves.

## 10 STATISTICS AND DATA ANALYSIS

### 10.1 Sample size calculation

The multicentre Evaluation of COPD Longitudinally to Identify Predictive Surrogate Endpoints (ECLIPSE) study reported the frequency of COPD exacerbation in 2138 patients [57]. For patients identical to our target population ( $\geq 2$  self reported COPD exacerbations in a year requiring antibiotics and/or OCSs), the mean (SD) number of COPD exacerbations within the subsequent one year was 2.22 (1.86), ([name], ECLIPSE statistician, personal communication). The Cardiac Insufficiency Bisoprolol Study II (CIBIS -II) reported that the proportion of participants who stop taking study medication in a trial of bisoprolol vs placebo to be about 15% and this is comparable with what has happened in TWICS [38].

Assuming a similar rate in the placebo arm 669 participants are needed in each arm of the trial to detect a clinically important reduction in COPD exacerbations of 15% (i.e. from an average of 2.22 to 1.89) with 90% power at the two-sided 5% significance level. Allowing for an estimated 15% withdrawal from study treatment the aim will therefore be to recruit 787 participants per arm (i.e. 1,574 in total).

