 For those participants who do not fulfil the  $FEV_1/FVC < 0.7$  at the time of testing despite a diagnosis of COPD, it is acceptable to conduct a slow vital capacity manoeuvre and to accept  $FEV_1/SVC < 0.7$ . If this criterion is not met historical evidence of,  $FEV_1/FVC < 0.7$  will be acceptable (however  $FEV_1 < 80\%$  predicted needs to be demonstrated at baseline – but see note 2 above, this is not a requirement during the COVID-19 pandemic).

 Spirometry equipment used should be maintained and serviced in line with manufacturer's guidelines.

 People with COPD were advised to shield in March 2020 due to COVID 19. These shielding arrangements remain in place to a greater or lesser degree, and many people are still partially shielding. Anecdotal evidence suggests that shielding reduced the number of exacerbations experienced by people with COPD. The ECLIPSE study has demonstrated that the frequent exacerbator phenotype is stable for at least 3 years. The modification of the inclusion criteria to include  $\geq 2$  exacerbations in any 12 month period since March 2019 enables the identification of the people at high risk of exacerbation during the time of reduced exacerbation risk during lockdown by combining exacerbations before and after the lockdown.

 There are a number of surgical procedures and other conditions after which spirometry is not recommended for a period of time. The table below is a pragmatic conservative adaptation of the recommendations of Cooper [44]. Other clinical or personal circumstances may preclude spirometry in individual cases. Such cases should be discussed with the study team. In cases where spirometry is contraindicated, entry into the trial should be delayed until the participant is able to perform spirometry.

| Surgical procedure/condition                                     | Notes about spirometry              |
|------------------------------------------------------------------|-------------------------------------|
| Thoracic/abdominal surgery                                       | 3 months post surgery               |
| Brain, eye, ear, ENT surgery                                     | 3 months post surgery               |
| Pneumothorax                                                     | 3 months post resolution            |
| Myocardial infarction                                            | 3 months                            |

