### **7.12 End of trial**

The end of clinical follow-up for each participant is defined as completion of the follow-up visit at 12 months. The end of clinical follow-up is when the last participant completes their follow-up visit at 12 months. The end of the trial is defined as the end of funding (currently 31 January 2023; but this may be extended and if so, a further amendment to protocol will be made).

The Funder, Investigators and/or the Trial Steering Committee have the right at any time to terminate the study for clinical or administrative reasons.

The end of the trial will be reported to the REC and Regulatory Authority within 90 days, or 15 days if the study is terminated prematurely. The Investigators will inform participants and ensure that the appropriate follow up is arranged for all involved.

A summary report of the trial will be provided to the REC and Regulatory Authority within 1 year of the end of the trial. An end of trial report will also be issued to the funders at the end of funding.

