### 10.3 Statistical analysis plan

Statistical analyses will be according to the intention to treat principle with a per protocol analysis performed as a sensitivity. The per protocol analysis will exclude participants who were not compliant (at less than 70%) with their study medication. All analyses will be governed by this comprehensive SAP which will be agreed by the Trial Steering Committee (TSC) and approved by the independent Data Monitoring Committee (DMC) prior to any analyses being undertaken. Unless pre-specified, a 5% two-sided significance level will be used to denote statistical significance throughout. There will be no interim analyses undertaken. In line with other recent COPD trials it is not envisaged that the DMC will be monitoring the study in order to terminate it prematurely on finding evidence of overwhelming benefit – nor will they terminate it for futility.

The primary outcome - number of COPD exacerbations requiring antibiotics and/or oral corticosteroids in the 12 months after randomisation - will be compared between randomised groups using negative binomial regression with length of time in the study as an offset. Estimates will then be adjusted for centre and other baseline covariates that are known to be strongly related to outcome (e.g. age, smoking, COPD hospitalisations in year prior to study – these will be pre-specified in the SAP). Despite the patients being followed-up for a single year, some will withdraw early and, given their chronic illness, some will inevitably die. Use of an overdispersion parameter should improve the model estimates as it takes between patient variability in exacerbation rate into account. The negative binomial model assumes that each patient has their own underlying exacerbation rate which follows a Poisson distribution, but the expected rate is allowed to vary across patients according to a gamma distribution. The shape parameter from the gamma distribution explicitly represents the variability between patients. The negative binomial model coincides with the Poisson model when this dispersion parameter is zero. Assumptions of this model are that exacerbation counts are assumed to vary about means that differ for each patient, with means varying across the population. Hence, the negative binomial model more effectively accounts for increased exacerbation events amongst patients withdrawing early.

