To further assess the impact of death (estimated at around 6% of the randomised subjects in the first 12 months after randomisation) on our potential treatment effect, a sensitivity analysis will be undertaken by excluding those subjects who have died. If there is any indication of a differential effect on deaths by treatment, models may be considered that allow the censoring to be informative. For participants that are lost to follow up at some time during the 12 month follow-up (estimated to be around 15% of those randomised), their information will be included in the statistical models up to the point that they are lost to follow up. Sensitivity analyses will be undertaken using multiple imputation (assuming data are missing at random), and, if necessary, and the data permit, specify the mechanism of missing data via a pattern mixture model assuming informative missingness.

The secondary outcomes - total number of COPD exacerbations requiring hospital admission and total number of emergency hospital admissions (all causes) - will each be analysed in the same way as for the primary outcome described above.

Disease related health status (measured using the COPD Assessment Test (CAT)), generic health-related quality of life (EQ5D-5L) and Hull Airways Reflux Questionnaire (HARQ), FEV1 and FVC are each measured at baseline, and at 6 and 12 month follow-up. A mixed effects model will be used to compare each outcome by randomisation group unadjusted and adjusted for centre, patient characteristics and/or baseline clinical variables. Mixed effects models assess rates of change with allowance for the correlation structure of the repeated measures data. Fixed effects will include assessment, treatment, centre and other relevant patient related variables and patient will be fitted as a random effect. A treatment-time interaction will be included to assess the differential treatment effect on rate of change in outcome. Alternative correlation structures will be considered and the most appropriate selected based on the log-likelihood and Akaike's Information Criterion (AIC) of the model. All randomised patients with at least one valid measurement will be included in the analysis and missing outcome data assumed to be missing at random.

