*As outlined previously in the protocol, the use of cardio-selective betablockers such as bisoprolol in people with COPD is safe. A systematic review of RCTs studying effects of cardio-selective blockers on lung function and respiratory symptoms in people with COPD demonstrated that the acute and chronic use of cardio-selective betablockers does not significantly reduce lung function, increase respiratory symptoms or reduce response to inhaled beta2 agonists. Moreover, since BICS started recruitment, a placebo controlled randomised clinical trial (BLOCK COPD) has reported that a year's treatment with the cardio-selective betablocker metoprolol (n=268) had no effect on lung function (FEV1) when compared with placebo (n=264). We have reviewed the dose titration data for BICS (maintaining the study blind): of the 429 participants recruited before recruitment was suspended, 49 had their dose of study medication reduced during dose titration because of a reduction in lung function (FEV1), with no significant difference between the two randomised study groups (9% vs 13%). In addition, for those who had the dose of study drug reduced during dose titration because of a reduction in FEV1, there was no difference in the absolute or relative reduction in FEV1 between the two randomised groups and only two of the 49 participants complained of intolerable breathlessness. It would appear that reductions in FEV1 during dose titration in BICS appear to be similar in magnitude and frequency between bisoprolol and placebo groups and do not manifest as increased symptoms.*

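### The 90% power at 787 per arm rests on unstated assumptions: stopping treatment is handled as missing patients although the analysis is ITT, and the expected loss to follow-up and deaths are not allowed for

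*Protocol*

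**What the plan says.** Section 10.1 takes a mean of 2.22 exacerbations (SD 1.86) in the following year from an earlier cohort, introduced as "For patients identical to our target population". It asks for 669 per arm to detect a fall to 1.89 "with 90% power at the two-sided 5% significance level". It then takes 15% as the share who stop study medication, citing an earlier bisoprolol trial, and says: "Allowing for an estimated 15% withdrawal from study treatment the aim will therefore be to recruit 787 participants per arm". The synopsis repeats this, and the sample-size section of Appendix 6 repeats the 90% figure.

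Section 10.3 states: "Statistical analyses will be according to the intention to treat principle". The primary outcome there is the count in the 12 months after randomisation, analysed by negative binomial regression with time in study as an offset. Sections 7.10 and 8.8 ask participants who stop treatment to remain in follow-up or, failing that under 7.10, to allow use of their records.

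Section 10.3 also gives an estimate for participants "lost to follow up at some time during the 12 month follow-up (estimated to be around 15% of those randomised" and expects around 6% deaths. Data up to the point of loss are kept. Section 7.6 adds a check of GP records for people who miss the 12-month assessment and do not complete the questionnaire.

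Note 5 of Section 6.1 explains why patients may now qualify on exacerbations since March 2019: "Anecdotal evidence suggests that shielding reduced the number of exacerbations experienced by people with COPD".

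**The concern.** Dividing by 0.85 is the right allowance when 15% of participants contribute no outcome data. Here the 15% are people who stop tablets, and the plan keeps them in the ITT comparison. Those in the bisoprolol arm then pull the average effect towards zero. That is a dilution of the difference, and a larger denominator does not correct for it in the same way. The losses that do remove information, loss to follow-up and death, are estimated in 10.3 but appear nowhere in 10.1.

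The placebo rate has a related problem. The source patients are still described as identical to the target population, although the entry criterion has since been widened because exacerbations were thought to have become less frequent.

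At stake is how a null result would be read. If the stated 90% is too high, a trial that finds no difference would be taken as stronger evidence against a 15% reduction than it is.

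**Working it through.** **Inputs from the protocol.** Mean 2.22, SD 1.86, target 1.89 (difference 0.33), two-sided 5%, 90% power, 15% stopping (all 10.1); 15% lost and 6% deaths (10.3); 1:1 allocation (7.3).

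**Reproducing the plan.** Two-means formula: n = 2(1.960 + 1.282)² × SD² / difference² = 2 × 10.507 × 3.4596 / 0.1089 = 668 per arm, against 669 stated. Power at 669 is Φ(0.33 / (1.86√(2/669)) − 1.96) = Φ(1.285) = 90.1%. Inflation: 669 / 0.85 = 787. Both figures stand.

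**Dilution, two-means method.** Assume no effect after stopping.
- Stopping at the outset: difference 0.85 × 0.33 = 0.2805. At 787 per arm, power = Φ(2.992 − 1.96) = 84.9%.
- Stopping spread evenly over the year: a stopper loses half the effect on average, so 1 − 0.15/2 = 0.925 is retained and the difference is 0.305. Power = Φ(3.255 − 1.96) = 90.2%.
- If a separate 15% also give no data (787 × 0.85 = 669 per arm): 78.8% and 85.1%.

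**Planned model.** Negative binomial dispersion from the stated SD: k = (1.86² − 2.22) / 2.22² = 0.2515. Information per arm is I = n Σ pⱼ / (1/(λtⱼ) + k), where pⱼ is the share of participants followed for time tⱼ. The standard error of the log rate ratio is √(1/I₀ + 1/I₁). The rate ratio is 1 − 0.15 × (share of effect retained): 0.8725 for early stopping, 0.861 for even stopping. For loss and deaths I let 21% contribute half a year. For early stopping this gives I₀ = 1,029, I₁ = 938, SE = 0.0451, and power = Φ(0.1364/0.0451 − 1.96) = 85.6%.

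Power at 787 per arm:

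| Stopping | Two-means, no loss | Two-means, separate 15% give nothing | Neg. binomial, no loss | Neg. binomial, 15% lost and 6% die at mid-year |
|---|---|---|---|---|
| Early, whole effect lost | 84.9% | 78.8% | 88.4% | 85.6% |
| Even over the year | 90.2% | 85.1% | 93.2% | 91.0% |
| No dilution | 94.1% | 90.1% | 96.3% | 94.8% |

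Simulations of the planned model with 15% loss and 6% deaths gave about 84 to 86% for early stopping and 90 to 92% for even stopping, in line with the last column.

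**Break-even.** To keep 90% without loss, about 92% of the effect must be retained under the two-means method (√(668/787)), or 87% under the negative binomial. With 15% lost at mid-year the negative binomial needs about 90%.

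**Lower placebo rates.** These are assumptions; the protocol gives only 2.22. Negative binomial, k held at 0.2515, loss and deaths as above:

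| Placebo rate | Early stopping | Even stopping | No dilution |
|---|---|---|---|
| 2.22 | 85.6% | 91.0% | 94.8% |
| 1.8 | 80.2% | 86.6% | 91.5% |
| 1.5 | 74.7% | 81.8% | 87.5% |

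**The case against.** The other side has a good deal.

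- The planned analysis is not a two-means test. It is more efficient with these inputs, and its power range straddles 90%.
- The protocol gives no timing for stopping, so inflating by 1/0.85² (669 / 0.7225 = 926 per arm) is right only if every stopper loses the whole effect from the start and is fully followed.
- Nothing says that the two 15% groups are different people. If they largely coincide and leave at the same time, there is little dilution: power is 90.1% (they give no data) to 92.3% (they give half a year, about 728 per arm) by two means.
- Data before loss are kept and GP records are a backup, so 79% is a lower bound for its scenario.
- The 15% is called a clinically important reduction and may already be meant as an ITT effect.

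All of this stands, and it narrows the point. It does not remove it, because the protocol states none of these conditions and its method reaches 90% only by counting stoppers as absent. Section 7.6 does describe the primary outcome as counted while on study medication, which would fit that method, but it conflicts with the 12 months after randomisation in 10.3.

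Two stronger readings are tempting. A reader might infer that the protocol says exacerbation rates have fallen. It reports only anecdotal evidence, and defends the new criterion by the stability of the frequent-exacerbator phenotype over at least 3 years. A reader might also set "of the 429 participants recruited before recruitment was suspended" against an end of trial "defined as the end of funding (currently 31 January 2023; but this may be extended" and conclude that 1,574 is out of reach. The documents do not support that: the end date may be extended, Section 10.2 says the projection will be updated, and no opening date is given from which to derive a recruitment rate.

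**Conclusion.** The concern holds as a gap in justification. It is not an arithmetic error, since 669 and 787 are both correct for the formula used, and it is not proof that the trial has less than 90% power. Section 10.1 makes one allowance, of the wrong kind for an ITT analysis, and makes none for the loss and deaths that 10.3 expects.

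At 787 per arm and a placebo rate of 2.22, power ranges from about 84 to 86% (stoppers lose the effect all year) to about 90 to 92% (stopping spread over the year) under the planned model with loss and deaths. The protocol's own method without loss gives about 85% and 90%. If the 15% is already an ITT effect, or stoppers and the lost largely overlap, 90% or more is kept at that rate. Lower placebo rates would reduce every figure, but how far is unknown.

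These results assume no effect after stopping, half-year average exposure for those lost or dying, and dispersion taken from the SD of 1.86. The statement should be corrected; the design itself is not in question.

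**What to change.** In Section 10.1, the synopsis and the Appendix 6 sample-size section, replace the single 90% figure with power for the ITT effect at 787 per arm under the negative binomial model:

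- treat stopping as dilution, with a stated assumption about its timing;
- treat loss to follow-up and death as reduced exposure, using the 15% and 6% from 10.3;
- state whether the 15% reduction is an ITT or an on-treatment effect, and whether stoppers and those lost are expected to overlap;
- describe the source cohort as similar to the population first targeted, in place of identical to it, and show power over placebo rates such as 1.5 to 2.22, labelled as assumptions.

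Reconcile the primary-outcome period in 7.6 with that in 10.3, since the answer decides how stoppers count.

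The cost is wording and a short calculation, and possibly a less favourable headline figure. Recruitment, conduct, analysis model and trial size do not change.
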